#### Passive Oddball Paradigm

Emotional and neutral words uttered by human voices recorded in stage 1 and synthesized voices created in stage 2 will be displayed to the participant. During the EEG recording, participants will sit on an armchair while watching a silent movie and will be instructed to pay no attention to the auditive stimuli. To facilitate the comparison of naturalness levels, six stimulus blocks will be created, each containing 600 stimuli corresponding to one of the five levels, or the human voice. Each block will consist of 480 frequently presented neutral-uttered standard stimuli (80%), and occasional 24 anger (4%), 24 disgust (4%), 24 fear (4%), 24 happiness (4%), and 24 sadness (4%) deviant stimuli. Standard and deviant stimuli will be equally uttered with a male, woman, or child voice. The stimuli will be presented pseudo-randomly with deviant stimuli being preceded by at least two standard stimuli. Each participant will listen to three blocks for an approximatively 30-min task. The stimulus sequences for each block will be fixed, and the order of blocks will be counterbalanced and randomized between participants. The stimulus onset asynchrony will be of 1,300 ms. The stimuli will be presented at 60 dB via the Shure SRH1840 audio headset that has a flat response frequency response in order to accurately reproduce the input audio signal. Autistic participants will be accompanied by their parent if necessary.

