##### Statistical analysis

The statistical significance of ERP components will be tested by comparing their mean amplitudes to zero at ROIs using one-sample t-tests. This method will allow us to focus exclusively on significant responses, and to distinguish significant scalp distributions from noise. Statistically significant ERPs will be considered for further amplitude analysis.

For standard stimuli, levels of naturalness comparisons will be performed by Level × ROI repeated measures ANOVAs on each ERP and group independently. For deviant stimuli, Level × ROI × Deviant repeated measures ANOVAs will be performed.

Group comparisons will be conducted by Group × ROI repeated measures ANOVAs on each ERP and level of naturalness separately, for standard stimuli. Similarly, for deviant stimuli, Group × ROI × Deviant repeated measures ANOVAs will be performed. The effect of reducing the naturalness of voice on emotion processing will be assessed by the comparison between ERPs amplitudes at levels 1–5 for ASD group and ERPs amplitudes calculated in the control group for human voices. We expect to detect less natural voices to help typical processing in ASD children, that is, fewer difference with non-pathological processing of human voices at least natural voices. Based on MMN analysis at maximum peak ROI, the voice leading to the nearest to non-pathological processing in autistic children will be chosen for Stage 3.

Scalp distribution comparisons for standard stimuli will be assessed by Group × Laterality (FP1, F3, F7, T7, C3, P3, P7, O1/AFz, Fz, CPz, Cz, POz, Pz/FP2, F4, F8, T8, C4, P4, P8, O2) repeated measures ANOVAs on each ERP and level of naturalness separately. For deviant stimuli, Group × Laterality × Deviant repeated measures ANOVAs will be conducted.

For all amplitude analysis, normality will be assessed by Shapiro–Wilk test. In case of non-parametric distribution of the data, a transformation will be applied. Mauchly’s test of sphericity will be used to evaluate homogeneity of variances and co-variances. In case of violation of sphericity, a Greenhouse-Geisser correction will be applied in order to test main effects significance. *Post hoc* comparisons will be conducted to assess specific differences (Tukey and Dunnett procedures). In all cases, level of significance will be set at *p* < 0.05 and statistical analysis will be performed with R software.

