#### Participants

Typically developed participants will be recruited from a public announcement posted on Tecnologico de Monterrey, Campus Monterrey. Autistic participants will be recruited by contacting parents of autistic children attending San Jose Hospital from Tecnologico de Monterrey.

Sample size estimation was calculated with G^∗^Power software version 3.1.9.7 (Faul et al., 2007) for Cohen’s d effect size index of 0.8, correlations among repeated measures of 0.5, statistical significance set at *p* < 0.05. For level comparisons, results indicated that 20 participants in each group would be enough to provide an estimated power of 0.90. For group comparisons, results indicated that 38 participants in each group would be enough to provide an estimated power of 0.91.

Forty high-functioning autistic volunteers aged 9 to 11-year-old will be involved in this stage of the research. All autistic participants will be diagnosed by a clinician according to DSM-V (Diagnostic and Statistical Manual of Mental Disorders, Fifth Edition) (American Psychiatric Association, 2013) or the International Classification of Diseases and Related Health Problems – Tenth Edition (World Health Organization, 1994) criteria. Autistic symptomatology will be assessed by the Autism Spectrum Rating Scales (ASRS) – parent report (Goldstein, 2012). A T-score greater than 60 (slightly elevated to very elevated scores for autistic behaviors) on Social/Communication, DSM-IV-TR (Text Revision), Peer and Adult Socialization and Social/Emotional Reciprocity domains will be considered as an inclusion criterion.

In addition, 40 TD volunteers aged 9 to 11-year-old will be included in this study. Similar to autistic children, ASRS will be used, and children with a score inferior to 60 in all scales will be included.

Any TD or autistic participant will be excluded if child:

•is under medication affecting the central or peripherical nervous system,•has hearing loss or deficits, and/or•has history of a developmental pathology and/or any disease affecting behavior and nervous system, apart from ASD for autistic participants.

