This project of investigation might encounter some pitfalls and unexpected results. Non-professionalism of actors recruited for emotional recordings during Stage 1 may affect the reliability of required prosodies. Nevertheless, the number of volunteers will be increased in order to generate four times more utterances than necessary to enable the selection of best actor participants. Furthermore, emotion recognition accuracy will be validated by supervised learning algorithm to ensure the quality of emotion discrimination based on acoustic features. Stage 2 aims to explore emotional recognition impairments in autism triggered by naturalness of human voices. We expect to observe a diminution of the amplitude of ERPs in the autistic population as a reflect of decreased attentional, sensorial, and cognitive emotional processing (Lartseva et al., 2015; Lindström et al., 2016, 2018). The autistic condition may also be characterized by hemispheric lateralization anomalies due to lateralized compensatory brain activity (Subbaraju et al., 2018). Impairments are expected to fade with the decreasing naturalness of voice stimuli. However, in the opposite case, no effect of naturalness on neural emotional processing by autistic children would be an evidence that the modulated acoustic parameters would not participate to autistic impairments. In the latter situation, or in case of enhancement of autistic impairments triggered by naturalness modulations, the acoustic edition of the stimuli will be reconsidered. Finally, Stage 3 expects the implementation of less natural voices in a robot-based intervention with the aim of improving emotion detection by autistic children. The 2-week intervention may imply a high rate of withdrawals whereas the sample size needed is relatively high. However, upon completion, we expect the intervention to trigger a reduction of autistic impairments (reduction of symptomatology, higher EEG activity, higher behavioral accuracy for emotion discrimination: smaller reaction times, and higher correct answers at end- and follow-up assessments).

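### The Discussion treats a null naturalness effect in autistic children as evidence that the edited acoustic parameters are not involved, but Stage 2 can exclude only large effects

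*Protocol article*

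**What the plan says.** The inference is in the Discussion, in the paragraph on pitfalls and unexpected results: "no effect of naturalness on neural emotional processing by autistic children would be an evidence that the modulated acoustic parameters would not participate" in autistic impairments. The same paragraph says that after a null or adverse result the editing of the stimuli will be reconsidered.

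The tools are in the Stage 2 Statistical analysis section: repeated measures ANOVAs with post hoc tests of difference. The threshold is p < 0.05 throughout ("In all cases, level of significance will be set at"). The section states no equivalence margin and no interval criterion.

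The same section describes the "comparison between ERPs amplitudes at levels 1–5 for ASD group and ERPs amplitudes calculated in the control group for human voices". It gives the expectation as "fewer difference with non-pathological processing of human voices at least natural voices". The rule for selecting the Stage 3 voice is given next, quoted here without its closing numeral: "Based on MMN analysis at maximum peak ROI, the voice leading to the nearest to non-pathological processing in autistic children will be chosen for Stage".

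For design and size:
- Passive Oddball Paradigm: six blocks (five levels and the human voice), and "Each participant will listen to three blocks for an approximatively 30-min task".
- Stage 2 Participants: 40 autistic and 40 typically developed (TD) children, with sample sizes at the 0.05 level based on these inputs: "Cohen’s d effect size index of 0.8, correlations among repeated measures of 0.5, statistical significance set at".

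**The concern.** A test of difference that does not reject shows absence of an effect only if the data also rule out effects that would matter. The Discussion sentence omits that second condition. The design is justified for detecting a large effect, and each voice level is heard by only about half of the autistic children. A null result could therefore arise easily while a moderate effect exists.

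If the sentence is followed as written, the edited features would be declared uninvolved in autistic impairments, and the stimuli reworked on that ground, when the data could not support either step. A smaller risk of the same kind concerns the selected voice. Its processing might be described as typical because a comparison with TD children was not significant.

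**Working it through.** **1. The plan's own sample size.** The Data Analysis section lists 18 ROIs. Take f = d/2 = 0.4, correlation 0.5, alpha 0.05 and the usual between-factor repeated measures formula, λ = N f² m / (1 + (m − 1)ρ), with m = 18.
- Group: 19 per group at a level, N = 38. λ = 38 × 0.16 × 18 / 9.5 = 11.52 and power is 0.910. Then 19 × 6/3 = 38 children per group, as stated (power 0.91).
- Level: 10 per level, six levels, N = 60. λ = 60 × 0.16 × 18 / 9.5 = 18.19 and power is 0.899. Then 10 × 6/3 = 20 children, as stated (power 0.90).

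The values of m and the 6/3 scaling are a reconstruction; the article does not give them. On this reading the stated sizes are correct for their purpose, which is detecting d = 0.8 averaged over ROIs.

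**2. Children per level.** 40 × 3/6 = 20 per group, if exposure is balanced.

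**3. Human voice versus level 1 in autistic children, one ROI.** Assume the best case: a balanced incomplete block layout with b = 40 children, k = 3 blocks each, v = 6 conditions and r = 20 children per condition, analysed within child.
- Children hearing any given pair: r(k − 1)/(v − 1) = 20 × 2/5 = 8.
- Error df: 120 − 40 − 6 + 1 = 75; t(0.975) = 1.992.
- Variance of a difference, with total SD 1: 2k(1 − ρ)/(8v) = 6(1 − ρ)/48 = 0.125(1 − ρ).

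| Within-child correlation | SE | 95% CI half-width | 0.5 SD missed | 0.8 SD missed |
|---|---|---|---|---|
| 0.5 (protocol's value) | 0.250 | 0.50 SD | 49% | 12% |
| 0.7 (assumed) | 0.194 | 0.39 SD | 28% | 2% |

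These miss rates come from the noncentral t distribution, two-sided 0.05, with no multiplicity correction. With 80% power the contrast detects 0.71 SD (correlation 0.5) or 0.55 SD (0.7).

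**4. Omnibus Level test, same layout.** The noncentrality is (8 × 6/3) Σ(τ − mean τ)² / (1 − ρ) = 16 Σ(τ − mean τ)² / (1 − ρ). For a linear trend with a 0.5 SD gap between the extremes, the sum is 0.175. At ρ = 0.5 this gives 5.6 on (5, 75) df, missed in about 62% of studies (39% at ρ = 0.7). The result depends on the pattern. A three-versus-three step is missed in 27% (6%), and a flat middle with two displaced extremes in 73% (55%). The Discussion expects impairments to fade as naturalness decreases, which is closest to the trend.

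**5. Autistic versus TD at one level, one ROI.** With 20 versus 20 the 95% CI half-width is 2.024 × √(2/20) = 0.64 SD. An observed difference of zero would still leave 0.64 SD open in either direction.

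**The case against.** **The sentence is discussion, not analysis.** It stands among anticipated pitfalls, names no test, and says no effect rather than no significant effect. Its stated consequence is only that the stimuli are revisited. This is fair and limits the practical harm. But difference tests at p < 0.05 are the only means the article gives for declaring no effect, and the sentence assigns evidential weight to that outcome. That is a stated inference, not a detail left to an analysis plan.

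**Power is better than single-ROI figures suggest.** Also correct. Averaged over 18 ROIs with 20 versus 20, the Group × ROI model has power of about 0.92 at d = 0.8 and 0.56 at d = 0.5. For the Level effect in autistic children, treating levels as independent groups of 20, power over 18 ROIs is 0.999 at f = 0.4 and 0.60 at f = 0.2. Large effects would therefore be found. Moderate ones would often not be, and 0.5 SD is an illustrative size that the article does not state.

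**The similarity limb.** A reader might infer that the plan declares typical processing, or picks the Stage 3 voice, from a failure to reject. The text does not support that. The phrase about fewer differences is an expectation. The operative rule picks the nearest voice, which is a ranking and needs no non-significant test. With balanced exposure, low precision does not by itself favour any one level. What remains is a caution about how the chosen voice is described.

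**Scope.** A reader might also take the sentence to say that the features play no part in autism. It speaks only of the edited parameters and autistic impairments. Nor does the article say that a null would be published as evidence against the mechanism.

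**Conclusion.** The concern holds for the Discussion sentence. With about 20 autistic children per level and tests of difference only, a null naturalness effect cannot count as evidence of non-involvement. At one ROI it misses a 0.5 SD human versus level 1 difference about half the time at the protocol's own correlation (28% at 0.7), with an interval half-width of 0.5 SD (0.4 SD). It excludes only large effects.

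This rests on balanced exposure to three of six blocks, a within-child analysis that uses the incomplete layout efficiently, no loss of children or epochs, and no multiplicity correction. Most departures from these would widen the interval. The sample size itself is not at fault for its stated aim, and the selection of the Stage 3 voice by ranking is not invalidated.

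**What to change.** - Reword the Discussion sentence: a non-significant naturalness effect is inconclusive. Report the human minus level 1 MMN difference in autistic children, with its 95% CI, at an ROI fixed in advance.
- Conclude that the edited parameters are not involved only if the whole interval lies inside a margin fixed before the data are seen. The margin must not be derived from the autistic-TD difference in the same sample, because it would then carry that sample's error.
- Report the Stage 3 voice as the nearest by ranking, with its autistic minus TD (human voice) difference and 95% CI. Do not call its processing typical because a test was not significant.

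No extra children or recordings are needed to make these changes. The price is that a null Stage 2 will usually be reported as inconclusive. If the true difference were zero, the 95% CI in step 3 would lie within an illustrative 0.5 SD margin in only about 6% of studies at correlation 0.5 (45% at 0.7). For a margin as wide as 0.8 SD it would do so in about 77% (97%). The investigators need to justify the margin on substantive grounds, and a demanding one cannot be met at this size.

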## Conclusion

The present research project aims to contribute to the current scientific knowledge by expecting to fulfil the following novel goals: (1) an emotional speech database adapted to the Mexican cultural shape of prosodic expressions will be created, (2) naturalness in voice will be defined and evidence that it triggers difficulty to discriminate emotional prosodies in ASD will be empirically supported, (3) a Social Stories^TM^ and robot-based intervention will be implemented to test the efficacy of using less-natural voices to help typical emotional discrimination in autistic children.

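### Stage 2 expects an ASD-specific effect of voice naturalness, but no planned model contains both Group and Level, and the stated assessment cannot separate it from an acoustic shift common to all children

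*Protocol article*

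**What the plan says.** The Conclusion states, about naturalness in voice, that "evidence that it triggers difficulty to discriminate emotional prosodies in ASD will be empirically supported". The Discussion gives the expected pattern: "Impairments are expected to fade with the decreasing naturalness of voice stimuli". Just before that, it describes the impairment as reduced ERP amplitude in the autistic population.

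The Stage 2 Statistical analysis section fixes these models:

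- Levels, standard stimuli: "levels of naturalness comparisons will be performed by Level × ROI repeated measures ANOVAs on each ERP and group independently".
- Levels, deviant stimuli: "For deviant stimuli, Level × ROI × Deviant repeated measures ANOVAs will be performed".
- Groups, standard stimuli: "Group comparisons will be conducted by Group × ROI repeated measures ANOVAs on each ERP and level of naturalness separately".
- Groups, deviant stimuli: "for deviant stimuli, Group × ROI × Deviant repeated measures ANOVAs will be performed".
- Scalp distribution: Group × Laterality "repeated measures ANOVAs on each ERP and level of naturalness separately. For deviant stimuli, Group × Laterality × Deviant repeated measures ANOVAs will be conducted".

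The effect of reducing naturalness is to be judged by the "comparison between ERPs amplitudes at levels 1–5 for ASD group and ERPs amplitudes calculated in the control group for human voices". The Stage 2 Participants section gives power for level comparisons (20 per group, 0.90) and for group comparisons (38 per group, 0.91), and plans 40 per group. Under Passive Oddball Paradigm, each child hears three of the six blocks (five levels and the human voice).

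**The concern.** An impairment is a difference from TD children. If it fades as naturalness falls, the difference between the groups depends on the level, which is a Group × Level interaction. An analysis split by group estimates how level acts in each group, and one split by level estimates the gap at each level. Neither tests whether the gap changes.

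The one assessment aimed at the question compares two cells that differ in both group and voice. A change in the ERP that the edited sound produces in any listener would then count as normalisation in autistic children. This is plausible: the stimuli are edited in spectrum, intensity and duration together (Creation of Five Levels of Naturalness for Emotional Speech), and the Introduction describes the MMN as an index of early discrimination of acoustic change. At stake is whether the Conclusion's statement about autism can be supported at all by the analysis as written.

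**Working it through.** **1. Which factors each analysis contains**

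| Stage 2 analysis | Group | Level |
|---|---|---|
| Level × ROI (× Deviant) | split by group (standards); no Group term (deviants) | yes |
| Group × ROI (× Deviant) | yes | split by level (standards); no Level term (deviants) |
| Group × Laterality (× Deviant) | yes | split by level (standards); no Level term (deviants) |
| Autistic children, levels 1–5, vs TD, human voice | changes | changes at the same time |

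No row yields a Group × Level term.

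**2. What the direct assessment can mistake (assumed values, in SD units)**

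TD on human voice = 0. Autistic children on human voice = −0.8. Editing to level 1 adds 0.8 in every child.

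- Autistic children at level 1: −0.8 + 0.8 = 0, equal to TD on human voice, so apparently normalised.
- TD at level 1: 0 + 0.8 = 0.8, so the gap at level 1 is still 0.8.
- Interaction: [0 − (−0.8)] − [0.8 − 0] = 0.

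**3. The plan's own power figures**

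Inputs: d = 0.8, taken as f = 0.4; correlation 0.5; alpha 0.05; m = 18 ROIs, counted from the Stage 2 Data Analysis section; half of each group at each level, because each child hears three of six blocks. Noncentrality: λ = f²·N·m / [1 + (m − 1)·0.5].

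- Group comparison, 38/2 = 19 per group per level, N = 38: λ = 0.16 × 38 × 18 / 9.5 = 11.52; power 0.910 (stated 0.91).
- Level comparison, 20/2 = 10 per level, six levels, N = 60: λ = 0.16 × 60 × 18 / 9.5 = 18.19; power 0.899 (stated 0.90).

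Both figures are reproduced as separate group and level tests, so neither covers the interaction.

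**4. Power of the missing term with 40 per group**

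The document gives no interaction size, so these are assumptions: the 20 possible sets of three blocks used equally, unit SD, within-child correlation 0.5, one amplitude per child and block, interaction linear over the six ordered voices.

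Each voice is heard by 20 children per group. Information per cell is within-child 0.8 × 20 / 0.5 = 32 plus between-child 0.2 × 20 / 2 = 2, total 34, where 0.8 is the block efficiency 6·2/(3·5). Over 12 cells, λ = 34 × 12 × f² = 408f².

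| Interaction f | λ | F(5,150) power | 1-df trend power |
|---|---|---|---|
| 0.10 | 4.08 | 0.29 | 0.52 |
| 0.20 | 16.32 | 0.88 | 0.98 |
| 0.25 | 25.50 | 0.98 | >0.99 |

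For scale, under a linear pattern the change in gap between the two extreme voices is 5.86f. A 0.8 SD gap that closes completely is therefore f = 0.8/5.86 = 0.137, λ = 7.62, with power 0.52 (F) and 0.78 (trend). The single contrast between the extreme voices has SE √(4/34) = 0.34 SD and power 0.64 for 0.8 SD.

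With the gain from averaging over ROIs that is implicit in step 3 (18/9.5 = 1.895), F power is 0.53 at f = 0.10 and 0.995 at f = 0.20, and the 0.8 SD contrast has 0.89.

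**The case against.** The strongest defence is that the operational aim is normalisation: to bring autistic children's responses close to TD responses to the human voice. For that aim TD on human voice is the intended reference, and the Level × ROI analysis in the autistic group shows whether naturalness affects them at all. This stands for the narrower aim. It does not carry the Conclusion, which attributes the autistic difficulty to naturalness.

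The by-level group tests do use the TD response to the edited voices, and in the example above they would probably show the persisting gap (reconstructed power 0.92 with 20 per group per level). But the plan does not make its statement about naturalness depend on them, and a set of separate tests does not estimate how much the gap changes.

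Two stronger readings are tempting and are not supported:

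- A reader might infer that the plan will take significance in autistic children alone as proof. No such rule is stated. At the design effect with 40 per group (20 per level), reconstructed power is 0.999, so an identical level effect would give that pattern with probability of only about 0.1%.
- A reader might infer that Stage 3 rests on this conclusion. The Stage 3 voice is chosen by how near the MMN in autistic children comes to TD processing of the human voice, which needs no interaction. Groups 1 and 2 of Stage 3 then compare synthesized with human voices directly.

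**Conclusion.** The concern holds for the ASD-specific reading of the Conclusion and Discussion. As written, Stage 2 contains no test of Group × Level, and its direct assessment cannot tell an ASD-specific effect from an acoustic shift common to both groups. This is not detail left to an unseen analysis plan, because the article names the models and how they are split. The stated power figures are not wrong; they answer other questions.

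The gap is in the inference, so its size is not an error rate: in the worked case the apparent normalisation is 0.8 SD and the true interaction is zero. The planned 40 per group would suit a moderate interaction (f about 0.20) but not a small one (f = 0.10), given the assumed correlation, balance of blocks and linear pattern.

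**What to change.** In the Stage 2 Statistical analysis section, add for each ERP one mixed model with Group × Level (× ROI, and × Deviant for deviant stimuli) over the five levels plus human voice. Include a random child effect, because each child hears only three of six blocks. Base the Conclusion's statement on the Group × Level term. An ordered trend can be a secondary contrast; it should not be the only test, since the Discussion leaves open up to which degree of removal helps. Keep the separate ANOVAs as follow-up and the MMN-based voice selection as planned.

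If the authors prefer not to add the model, limit the Conclusion to saying that reduced naturalness brings autistic children's responses closer to TD responses to the human voice.

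Cost: a change of analysis text before data are collected, with no extra recordings, since both groups already hear the edited voices. The downside is power. The interaction has less power than the main effects and is outside the Stage 2 power statements, so the Participants section needs a sentence giving the interaction size that 40 per group can detect and the assumptions behind it.
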